**2. Drug packaging**

Drugs to be used in the test group and control group are in identical packaging, and their labels shall be printed with the contents including the actions and indications, usage and dosage, lot number, drug suppliers, drug code, etc., and marked with “drugs for clinical trial” and “only for clinical research”. The bottle, box and label of the investigational drug, control drug and simulators are identical.

No.1 medication and No.2 medication are respectively packaged in two bottles, determined by calculation after dose adjustment. Medications for each visit cycle should be prepared according to the maximal doses that may be administered. Medications for 48 weeks are packaged in a big package. Blind coding is performed according to the random allocation table, and each big package is marked with a drug code from 1-800.

**3. Drug distribution**

Sub-packed kits are sent to each test center according to their randomly assigned number of the test center, along with the corresponding emergency letter, for multi-center clinical trial.

**4. Medication method**

**Study group:**

No. 1 medication: Xiaoke Pills, the initial dose of 5 pills, once daily, p.o.; the maximal daily dose of 30 pills, 3 times daily, p.o.

No. 2 medication: Simulator of glibenclamide tablets, the initial dose of 0.5 (1.25 mg) tablet/day, p.o.; the maximal daily dose of 3 (7.5 mg) tablets/day, 3 times daily, p.o.

**Control group:**

No. 1 medication: Simulator of Xiaoke Pills, the initial dose of 5 pills, once daily, p.o.; the maximal daily dose of 30 pills, 3 times daily, p.o.

No. 2 medication: Glibenclamide tablets, the initial dose of 0.5 (1.25 mg) tablet/day p.o.; the maximal daily dose of 3 (7.5 mg) tablets/day, 3 times daily, p.o.

In addition to the above study drugs, patients treated with Metformin, either in the test group or the control group should also take metformin tablets orally at a dose the same as that at enrollment, while the dose remain the same throughout the trial.

Medication period: 48 weeks.

**6. Drug inventory and preservation**

The number, shipment, delivery, transition, storage, distribution, recycling, and destruction of study drugs should all be recorded. The records are preserved as the clinical trial documents.

After arrived at each clinical trial center, all study drugs should be submitted to designated personnel and managed at the designated place that meets the requirements of drug storage, and released by designated personnel do not participate in the clinical trial.

Trail managers should regularly check the quality of the drugs.

It only allows the investigators to use the study drugs, and the investigators must ensure that all drugs are only used in subjects enrolled in the clinical trial, and are used strictly in accordance with the clinical trial protocol.

The investigators should recover the remaining drugs at each return visit. After the clinical trial is completed, designated personnel from the sponsor should recover all the remaining study drugs in time.

**7. Combination therapy**

During the trial, the subjects should not use other Chinese herbs or western medicine or other therapies of hypoglycemic effects. For original or newly occurred concomitant diseases (e.g., hypertension) that require medication, the combination therapy should be recorded in details in the combination therapy registration form.

## VII. Monitoring indicators

**1. Conventional indicators**

Blood and urine routine tests, liver and kidney function, blood glucose, insulin, C peptide, glycosylated hemoglobin (HbA1c), blood lipids, inflammatory factors (hsCRP), adiponectin, ECG, weight, blood pressure;

Cardiovascular complications: angina pectoris, myocardial infarction, death. The occurrence of other chronic complications of diabetes (e.g., microalbuminuria).

The incidence of hypoglycemia and other clinical adverse events (patients test their blood glucose at home using glucose meter and record the test results in the blood glucose record card.)

Score of TCM symptoms of diabetes and Pattern of dual deficiency of Qi and Yin: including the main symptoms, secondary symptoms.

Select 100 patients for brachial artery ultrasonography to evaluate whether the Xiaoke Pills has the effects on blood vessel endothelial function.

**2. Pharmacogenetics study**

2.1`Collect 10 ml of peripheral blood sample from the patients, and use phenol-chloroform method to extract genomic DNA.

2.2 Use high-throughput SNP technologies to detect the gene polymorphism of the major targets of glyburide and drug metabolism-related proteins, including sulfonylurea receptor, potassium channel protein Kir6.2, genes associated with βcell function, CYP2C9. Use the above symbolic or “node” protein or molecule and the key molecules of the action and metabolic pathways of biguanides and sulfonylureas as candidate genes to make SNPs biochip, use technologies of genomic detection and analysis platform to detect these SNPs sites, analyze the interactions between SNPs, to establish the correlation between different drug responsiveness and SNPs, so as to identify the SNPs sites that can guide personalized therapy in clinical practice.

**3. Metabonomics study**

Collect the urine samples of baseline and follow-up at each stage of the trial for testing and analysis of the metabolites. Establish and apply high-throughput, hypersensitized metabolomics detection and analysis technologies, including electron paramagnetic resonance spectrometer, LC and GC-MS as well as automatic biochemical analyzer, combined with laser copolymer fluorescence microscopy and other molecular cytobiology and immunology technologies for testing and analysis of the clinical samples of these populations, in particular the trace and rapid decayed metabolic regulation signaling molecules, metabolites of glibenclamide and the Chinese herbal ingredients in Xiaoke Pills; through qualitative and quantitative analysis, identify the metabolic molecules of specific abnormalities (high or low) to obtain the analysis spectrum of related metabolic molecular, so as to determine the most representative and original corresponding indicators that can accurately reflect the therapeutic response.

**Appendix 1:**

**Score of TCM symptoms of diabetes**

(modified from “guiding principle for clinical study of new Chinese medicine treating diabetes” recorded in the book of *Guiding Principles for Clinical Study of New Chinese Medicinal*, Chinese Medical Science and Technology Publishing House, May, 2002, the first edition)

**Main symptoms:** dry throat and mouth, lack of strength.

**Secondary symptoms:** polyphagia, polydipsia, shortness of breath, vexing heat in the chest, palms and soles, palpitations, insomnia, reddish urine, and constipation

| **symptoms** | **Slight（1 point）** | **moderate（2 points）** | **severe（3 points）** |
| --- | --- | --- | --- |
| Dry throat and mouth | Slightly | Occasionally | obviously |
| Fatigue | Can not stand hard work | Able to do light work | Barely for daily activity |
| Polyphagia and easily hungry | Obviously hungry | Unable to stand hungry before meal | Unable to stand hungry and easily accompanied with hypoglycemia |
| Thirsty for drink | Slightly increased of drinking water | Increased amount of drinking water | Double increased of drinking water |
| Short of breath, lazy to talk | Short of breath after laboring | Short of breath after normal activities | Lazy to talk, short of breath all the time |
| Vexation | Occasionally occurred | Vexation | Vexation and sleeplessness |
| Feverish palms and soles | Feverish palms and soles | Feverish palms and soles, like uncovering coat | Like holding cold objects |
| Palpitation | Occasionally occurred | Often occurred, lasting short time | Often occurred, lasting long time |
| Insomnia | Short of sleep and easily wake up | Hard to sleep, and easily wake up | Hard to sleep for the whole night |
| Constipation | Dry stool and hardly defecate | Dry stool and one defecation in 2-3 days | Dry stool and one defecation in more than 3 days |

Note: Score as “0” if there are no symptoms

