**2. Trial goals**

2.1 To discover biomarkers related to the clinical efficacy of Xiaoke Pills with glibenclamide as a reference.

2.2 To discover biomarkers related to the main side effect, i.e., hypoglycemia and study pathophysiological and clinical features of susceptibility to hypoglycemia.

2.3 To discover the unique efficacy of Xiaoke Pills compared with sulfonylureas, as well as the biomarkers associated with the unique efficacy of Xiaoke Pills.

2.4 To discover biomarkers, pathophysiological and clinical features associated with secondary failure of sulfonylureas. To investigate if Xiaoke Pills can reduce the risk of secondary failure of sulfonylureas as compared with glibenclamide.

2.5 Apply the TCM evaluation indexes to evaluate the efficacy and safety of Xiaoke Pills and glibenclamide tablets from the view of treatment of type 2 diabetes belonging to the syndrome of dual deficiency of qi and yin, and to found the biomarkers associated with above evaluation indexes.

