**2. Secondary endpoints and indicators**

2.1 Incidence and rate of hypoglycemia;

2.2 General efficacy (FPG, 2hPG, HbAlc) and the efficacy of TCM Syndrome of dual deficiency of *qi* and *yin* ;

2.3 Proportion of patients with HbA1c < 6.5% at 48 week;

2.4 The time to achieve HbA1c <6.5%;

2.4 Changes in islet -cell function (HOMA-IS = 20 × FINS/(FPG-3.5));

2.5 Changes in insulin resistance levels (HOMA-IR = FINS × FPG/22.5);

2.6 Changes in weight, waist circumference, and hip circumference;

2.7 Changes in lipids levels, insulin levels, inflammatory factors (hsCRP), and adiponectin;

2.8 Metabolomics and pharmacogenetics;

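### The TCM symptom score in Appendix 1 is not sound as written: one listed symptom has no graded row, a main symptom has conflicting grade wording, and the top polyphagia grade includes hypoglycaemia

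*Protocol*

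**What the plan says.** Appendix 1 (Score of TCM symptoms of diabetes) names two main symptoms, "dry throat and mouth, lack of strength", and a list of secondary symptoms that includes "vexing heat in the chest, palms and soles" and ends with "palpitations, insomnia, reddish urine, and constipation". A table then grades each symptom under three columns: slight (1 point), moderate (2 points) and severe (3 points). An absent symptom scores 0. No row deals with reddish urine.

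The row for the first main symptom is "Dry throat and mouth | Slightly | Occasionally | obviously". A row lower down is "Palpitation | Occasionally occurred | Often occurred, lasting short time | Often occurred, lasting long time". The severe grade of polyphagia is "Unable to stand hungry and easily accompanied with hypoglycemia".

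The score is a monitoring indicator in Section VII.1, and the schedule of trial procedures has TCM symptoms assessed at every visit from week -4 to week 48. It feeds the secondary endpoint on "the efficacy of TCM Syndrome of dual deficiency of" qi and yin (Section III.2, item 2.2) and goal 2.5 in Section II.2. Hypoglycaemia is a separate secondary endpoint (item 2.1), and the trial goals name it as the main side effect: "To discover biomarkers related to the main side effect, i.e., hypoglycemia".

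**The concern.** The wording of the grades determines what is recorded at each visit, so an analysis plan cannot repair it afterwards.

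Three consequences follow.

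- **Reddish urine.** A site that follows the list expects to score it, and a site that follows the table cannot.
- **Dry throat and mouth.** This is one of only two main symptoms. A rater who goes by the column heading and one who goes by the cell wording can give the same patient different points. That adds noise. It can also record a change from occasional dryness to slight but constant dryness as an improvement from 2 to 1.
- **Polyphagia.** A low glucose caused by treatment can help move a patient into the worst grade of an efficacy item. If one arm has more hypoglycaemia, its TCM result would look worse for a reason that belongs to safety. Goal 2.2 looks for markers of hypoglycaemia and goal 2.5 for markers tied to the TCM indexes, so this grade could also let one kind of marker show up as the other.

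**Working it through.** The Protocol gives no total or range for this scale, so there is no stated figure to reproduce. The check matches the list to the table, compares grade wording across rows, and counts the points.

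**Step 1: list against table (Appendix 1).**

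| Listed symptom | Graded row(s) |
| --- | --- |
| Dry throat and mouth (main) | 1 |
| Lack of strength (main) | 1 (fatigue) |
| Polyphagia | 1 |
| Polydipsia | 1 (thirst) |
| Shortness of breath | 1 |
| Vexing heat | 2 (vexation; palms and soles) |
| Palpitations | 1 |
| Insomnia | 1 |
| Reddish urine | 0 |
| Constipation | 1 |

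There are 10 listed symptoms and 10 graded rows. The counts agree only because vexing heat is split over two rows while reddish urine has none.

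**Step 2: range.** The table as printed gives 10 × 3 = 30, so a total runs from 0 to 30. If reddish urine were graded like the rest, it would be 11 × 3 = 33, so 0 to 33.

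**Step 3: the dry-mouth grades.** The three cells run intensity, frequency, intensity. The column heading over the middle cell is moderate, which is an intensity. For palpitation and for vexation, occasional occurrence is the 1-point grade; for dry mouth it is worth 2. The cell therefore disagrees both with its own heading and with the rest of the table.

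**Step 4: the polyphagia grade.** Four facts from the Protocol bear on it.

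- Before randomisation, patients are either untreated or on metformin alone (Section V.1). The metformin package insert says that metformin alone generally does not cause hypoglycaemia in type 2 diabetes.
- After randomisation every patient receives glibenclamide. Each dose step holds 5 × 0.25 mg = 1.25 mg in the pills and 0.5 × 2.5 mg = 1.25 mg in the tablets (Sections VI.1 and VI.5).
- The classification of hypoglycaemic reactions in Section X lists hunger among the manifestations.
- The 3-point grade needs both marked hunger and proneness to hypoglycaemia, so a low glucose by itself does not score 3.

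Treatment can thus help bring a patient into this grade. Whether that tilts the comparison depends on whether the arms differ in hypoglycaemia.

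**Step 5: how much of the score is involved.** Dry mouth and polyphagia hold 3 points each: 6/30 = 20% of the printed maximum. Without polyphagia the range is 9 × 3 = 27.

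**Step 6: repair elsewhere.** Section XII.10 names source books for the symptom items but gives no grades. Section VII.1 says only that the score covers main and secondary symptoms. Neither resolves the three points.

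**The case against.** The strongest reply is that the scale works well enough. Ten rows carry 0 to 3 points and the column headings put every row in order. The form is adapted from a published guideline, and the odd dry-mouth wording may be a translation slip. The arms share glibenclamide content per dose step, titration rule and blinding, so the hypoglycaemia wording need not favour either. The only earlier count in the Protocol (Section I) is two mild events against one in a study of 450 subjects. Changing the form would also break comparability with the week -4 and week 0 scores.

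Much of this stands, and it rules out several stronger readings:

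- **That the scale cannot give a valid score.** A total of 0 to 30 can be added up, and the headings supply an order.
- **That 9% of the points cannot be scored.** That is 3/33, and the Protocol never states a maximum of 33. An item with no row adds nothing in either arm.
- **That the fatigue grades are invalid.** They read as falling capacity, from hard work to light work to bare daily activity, under ordered headings.
- **That the polyphagia grade biases the TCM result or counts events twice.** Between-arm bias needs a difference in hypoglycaemia, which is not known in advance. Endpoints 2.1 and 2.2 are not combined, so one event informing both is not double counting.
- **That goal 2.5 seeks a unique Xiaoke effect.** That aim is in goal 2.3. Goal 2.5 evaluates both drugs with TCM indexes.

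The reply does not remove the mismatch between list and table, or the conflict between the dry-mouth cell and its heading. Nor can equal hypoglycaemia be assumed, since comparing it is a secondary endpoint.

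**Conclusion.** The point holds as a correctable defect in the form that feeds the TCM part of secondary endpoint 2.2 and goal 2.5. One listed symptom of ten has no graded row. One of the two main symptoms has grade wording at odds with its heading and with the rest of the table. One 3-point grade includes the treatments' main side effect. The last two rows together hold 6 of the 30 available points.

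The size of any effect on the TCM result cannot be worked out from the Protocol. For dry mouth it depends on how sites read the cell. For polyphagia it depends on a difference in hypoglycaemia between arms; with none, the wording does not distort the comparison of arms. The conclusion assumes that the English text reflects the form in use, which should be checked. The primary HbA1c endpoint and the sample size do not depend on this score.

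**What to change.** 1. Add a graded row for reddish urine or delete it from the list, and state the total range (0 to 33 or 0 to 30).
2. Check the dry-mouth row against the original-language form, then word its three grades on one intensity dimension that matches slight, moderate and severe.
3. Keep the polyphagia item, and also report the TCM score without it as a sensitivity analysis (0 to 27 on the printed table). If no patient has yet been scored, removing the hypoglycaemia wording from the grade is an alternative.

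The cost is a small correction to the appendix and case report form, a note to sites, and one extra analysis. Grade wording changed after scoring has begun would break comparability with baseline. In that case leave the grades alone and use only the sensitivity analysis. That analysis removes the one grade that names hypoglycaemia. It does not remove every item that hypoglycaemia might touch, since Section X also lists palpitations among its manifestations.

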## VIII. Evaluation of clinical efficacy and of relevant laboratory test results

1. The proportion of patients reaching the endpoint at 3 months, 6 months, and 9 months.

2. FPG, 2hPG, HbAlc.

3. The percentage of patients with HbA1c reaching the standard (6.5%) at 3 months, 6 months, and 9 months.

4. The incidence of hypoglycemia and other complications of diabetes.

6. Laboratory indicators: changes in blood lipid levels, insulin levels, C-peptide level, inflammatory factors (hsCRP), adiponectin.

7. Changes in islet -cell function (HOMA-IS = 20 × FINS/(FPG-3.5)).

8. Changes in the levels of insulin resistance (HOMA-IR = FINS × FPG/22.5).

9. Genomic and metabolomic studies.

Analyze a large number of SNP and metabolic data to reveal the major genetic andmetabolic that impact the drug efficacy.

## IX. Follow-up plan

A 4-weeks run-in period, 13 times of followed up every 4 weeks after randomization for a total of 48 weeks.

**1. Preliminary screening before the run-in period**

1.1 The patients sign the informed consent and accept the screening.

1.2 The history and diagnosis: history, previously extent underlying diseases, combined medications, Western medical diagnosis and TCM pattern.

1.3 Physical Examination: To measure the height, weight, waist circumference, hip circumference, and vital signs.

1.4 Laboratory indicators: blood and urine routine tests, liver and kidney function tests, fasting blood glucose, detection of HbA1c.

1.5 If all the above items meet the case selection criteria, the patient will be assigned to screening number, and enter a 4-week run-in period.

**2. Baseline inspection items**

2.1 After the end of the run-in period, if all the items still meet the case selection criteria, patients will be randomly assigned to a case number, which remains unchanged during the entire course of the study.

2.2 Carry out the fasting plasma glucose, standard postprandial 2h plasma glucose, HbA1c, plasma insulin, blood C-peptide, inflammatory factors (hsCRP), lipids, adiponectin, urinary albumin-to-creatinine ratio, 12-lead ECG examinations.

2.3 Collect 10 ml of anticoagulated blood for extraction of DNA, and 10 ml of urine for metabonomic study.

2.4 Evaluation of TCM symptoms (TCM Hospitals).

2.5 Distribution of study drugs.

2.6 Additional examinations to be taken in TCM Hospitals: 100 cases to receive the brachial artery color Doppler ultrasonography; nocturia index (nocturia volume/24-hour urine volume, daily urine: urine volume from 8:00 a.m. to 8:00 p.m., nocturia: urine volume from 8:00 p.m. to 8:00 a.m.)

**3. Items to be followed-up at every 4 weeks**

3.1 Evaluation of TCM patterns (TCM Hospitals) and the incidence of hypoglycemia in the past 4 weeks;

3.2 Fasting plasma glucose;

3.3 Weight, waist circumference, hip circumference;

3.4 Collect 10ml urine for metabonomics study.

**4. Items to be followed-up every 12 weeks**

4.1 fasting insulin, C peptide, glycosylated hemoglobin (HbA1c);

4.2 lipids, inflammatory factors (hsCRP), adiponectin;

**5. Items to be tested at the** 24th **week**

5.1 Blood and urine routine tests, liver and kidney function tests;

5.2 nocturia index (nocturia volume/24-hour urine volume);

5.3 12-lead ECG.

**6. Items to be tested at the 48th week**

Standard postprandial 2-hour blood glucose, urinary albumin-to-creatinine ratio, blood and urine routine tests, liver and kidney function tests, 12-lead ECG, blood lipids, C-peptide, insulin, inflammatory factors (hsCRP), adiponectin; 100 cases to receive additional examination of brachial artery color Doppler ultrasonography in TCM Hospitals, patients will undergo willundergo the brachial artery color Doppler ultrasonography once again, nocturia index (nocturia volume/24-hour urine volume) will also be obtained .

Items to be measured at Central laboratory include HbA1c, C-peptide, insulin, blood lipids, C-peptide, insulin, inflammatory factors (hsCRP), adiponectin. Intravenous blood for measurement will be drown, processed according to SOP and shipped to the central laboratory.

## X. Adverse events

**1. Definition**

1.1 Adverse Events: refer to adverse medical events occur after patients or subjects of clinical trials treated with a drug, which do not necessarily have a causal relationship with the treatment.

1.2 Serious adverse events: events occurred during clinical trials requiring hospitalization, prolonged length of hospital stay, disability, affecting the work ability, endangering the life or leading to death, resulting in congenital malformations.

1.3 Adverse drug reactions: refer to harmful, unexpected reactions which have a causal relationship with the application of the drug occurred during the process of normal application of a drug at a dose in line with the requirements. In a clinical trial of a new drug or new usage of a drug, when the therapeutic dose has not been established, all the harmful, unexpected reactions which have a causal relationship with the application of the drug should be considered as adverse drug reactions.

1.4 Hypoglycemia: patients with hypoglycemia will record the episodes of hypoglycemia, blood glucose levels, concomitant symptoms and the treatment in the study diary card provided by the sponsor.

1.4.1 The episode of hypoglycemia is defined as the patient feel that he/she has the signs or symptoms associated with hypoglycemia at any time, or with blood glucose <63 mg/dL (3.5 mmol/L) [IFCC  plasma:<68 mg/dL (3.8 mmol/L))], even if not accompanied by symptoms, signs or not requiring treatment.

1.4.2 Severe hypoglycemia is defined as the patient has onset of symptoms related to hypoglycemia and need help from others, with blood glucose < 50 mg/dL (2.8 mmol/L) [IFCC plasma: <55 mg/dL (3.0 mmol/L) ] or immediately recovered after oral administration of carbohydrate or glucagon or intravenous injection of glucose.

1.4.3 The definition on blood glucose levels of nocturnal hypoglycemia is similar (for example: hypoglycemia is <63 mg/dL, severe hypoglycemia <50 mg/dL), which is according to the adverse event reports and blood glucose levels of the patients. Nocturnal hypoglycemia is defined as the event that occurs before the 1st meal (e.g. breakfast) after wake up from falling sleep.

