So far, the results of five RCTs compared Xiaoke Pill and glibenclamide were reported in medical journals in China. All studies were open label with study duration between 4 to 8 weeks. Four studies were done in single center ones. All study showed significant improvement in diabetes symptoms in favor of Xiaoke Pill. Instead using absolute changes in glucose and HbA1c, all trails used proportion of glucose or HbA1c below certain levels as the indicators of efficacies. Two 4 week studies comparing HbA1c, fasting glucose and postprandial did not find differences between Xiaoke Pill and glibenclamide. Three 8 week studies comparing fasting glucose found Xiaoke Pill was associated with significant greater improvement in fasting glucose control as compared with glibenclamide. Only one study assessed hypoglycemia event (450 study subjects, two mild hypoglycemia events in Xiaoke pill group, one in glibenclamide group). The poor qualities of these clinical trials make it hard to draw any solid conclusions with regard to efficacy and safety of Xiaoke pill. However, the validity of the design of these studies is questionable, and makes it hard to draw any robust conclusion with regard to safety and efficacy of Xiaoke Pill.

Therefore, in order to better guide the clinical application of Xiaoke Pills containing glibenclamide ingredients, improve the efficacy of medication, reduce the adverse drug reactions, and understand the differences between Xiaoke Pills and pure glibenclamide preparations in clinical efficacy, adverse drug reactions and biological basis, this project intends to explore the effect of genetic, metabolic background as well as their mechanisms in determining the differences in response to Xiaoke Pills and glibenclamide so as to provide basis for the development of personalized therapy plan for different type 2 diabetic patients to improve the efficacy of Xiaoke Pills, and to establish clinical treatment regimen of Xiaoke Pills based on molecular typing.

2. Personalized therapy of diabetes

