## V. Case selection criteria

**1. Inclusion criteria**

1.1 Patients with type 2 diabetes;

1.2 Belonging to TCM Syndrome of dual deficiency of *qi* and *yin*;

1.3 Aged 21～70 years;

1.4 Patients for initial treatment: Patients who have not received any hypoglycemic agent and are non-obese,, with body mass index (BMI) within 18kg/m2 ~ 28 kg/m2 (not included);

1.5 Patients treated with metformin: Patients have received treatment with metformin (immediate-release) at a stable dose ≥ 750 mg/day for at least 3 months before screening, with body mass index (BMI) within 18kg/m2 ~ 35 kg/m2 (not included);

1.6 Body weight remains constant (body weight fluctuates by less than 10% within at least 3 months before screening);

1.7 Poor glycemic control, fasting blood glucose greater than 126 mg/dl (7.0 mmol/L) and HbA1c >7.0% (preliminary screening), fasting blood glucose greater than 126 mg/dl (7.0 mmol/L) (after run-in);

1.8 Patients still meet the above criteria (without considering HbA1c) after a 4-week run-in period.

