**Classification of hypoglycemic reactions:**

| **Classification** | **Clinical manifestation** | **Treatment** |
| --- | --- | --- |
| Hypoglycemia | Tachycardia, palpitations, trembling, sweating, hunger, dizziness, blurred vision, impaired concentration, behavior disorders, etc. Patients do not need assistance from others, and can take the initiative to seek treatment. Or blood glucose <63 mg/dL (3.5 mmol/L) [IFCC plasma :< 68 mg/dL (3.8 mmol/L)], even if not accompanied by symptoms, signs or not requiring treatment. | Rapid remission after eating carbohydrates |
| Severe hypoglycemia | Hypoglycemia leads to manifestations such as coma, seizures or nervous system damage, and the patient cannot take the initiative to require treatment or seek help. Accompanied by blood glucose < 50 mg/dL (2.8 mmol/L) [IFCC plasma: < 55 mg/dL (3.0 mmol/L)] | Requiring intravenous bolus injection of glucose or glucagon injection for emergency treatment |
| Nocturnal hypoglycemia | Nocturnal hypoglycemia refers to the event that occurs before the 1st meal (e.g. breakfast) after wake up from falling sleep, presenting with clinical manifestations and blood glucose values of hypoglycemia or severe hypoglycemia | Mild patients should take food, while severe patients need intravenous injection of glucose |

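### Non-severe hypoglycaemia counts on felt symptoms alone, and two of those symptoms also belong to the syndrome required for entry, so endpoint 2.1 and the goal 2.2 phenotype need a glucose-confirmed class

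*Protocol*

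**What the plan says.** **Definition.** Protocol X.1.4.1 offers two routes to an episode. The first is "The episode of hypoglycemia is defined as the patient feel that he/she has the signs or symptoms associated with hypoglycemia at any time". The second is joined as an alternative: "or with blood glucose <63 mg/dL (3.5 mmol/L" (the plasma equivalent given is 3.8 mmol/L). The classification table in section X repeats both routes for the non-severe class and lists "Tachycardia, palpitations, trembling, sweating, hunger, dizziness, blurred vision, impaired concentration, behavior disorders, etc" as its manifestations. Severe hypoglycaemia is defined more tightly: X.1.4.2 needs help from others together with a low glucose or prompt recovery.

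**Population.** Inclusion criterion 1.2 (section V.1) reads "Belonging to TCM Syndrome of dual deficiency of" qi and yin. Appendix 1 gives the secondary symptoms as "polyphagia, polydipsia, shortness of breath, vexing heat in the chest, palms and soles, palpitations, insomnia, reddish urine, and constipation". Its scale has an item for polyphagia and being easily hungry, whose severe grade is "Unable to stand hungry and easily accompanied with hypoglycemia".

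**Use.** Incidence and rate of hypoglycaemia is item 2.1 of the secondary endpoints (section III.2). Trial goal 2.2 (section II.2) seeks biomarkers of hypoglycaemia. Section XII.8 leaves the between-group comparison to the statistical analysis plan, which is not at hand.

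**Recording.** Under X.1.4 patients enter episodes, glucose levels, symptoms and treatment on a diary card, and section VII.1 provides for home meter testing. In the schedule of procedures, hypoglycaemia is recorded from week 4, while TCM symptoms are scored from week -4.

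**The concern.** A patient enrolled with palpitations or frequent hunger may continue to have them on treatment and, knowing that the drug can lower glucose, log them as hypoglycaemia. Under the definition these entries count the same as a measured low glucose. Three things are at stake.

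1. **Dilution.** Symptom-only entries unrelated to glucose pull a real difference between arms towards no difference, whichever arm it favours.
2. **Bias, conditional on symptom relief.** Both arms step glibenclamide in equal amounts (5 pills at 0.25 mg each is 1.25 mg, or half a 2.5 mg tablet) under the same fasting-glucose rule, so the planned difference is the herbs. Section I.1 says of the earlier trials: "All study showed significant improvement in diabetes symptoms in favor of Xiaoke Pill". If that extends to palpitations and hunger, Xiaoke Pills would show fewer episodes without any effect on glucose. Blinding does not remove a real drug effect on the mimicking symptoms.
3. **Phenotype.** For goal 2.2, cases would mix patients with low glucose and patients with syndrome complaints.

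The overlap also runs the other way, since true hypoglycaemia can raise the hunger and palpitation items of the TCM score.

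**Working it through.** **No plan figure to reproduce.** The protocol states no rate, power or sample size for hypoglycaemia. Its only calculation is for HbA1c, and nothing here depends on it.

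**Extent of overlap.** The table lists nine manifestations for non-severe hypoglycaemia. Two of them, palpitations and hunger, are in Appendix 1 (three if tachycardia is read with palpitations). Both are secondary symptoms. The main symptoms, dry throat and mouth and lack of strength, are not in the hypoglycaemia table. Trembling, sweating, dizziness and blurred vision are not in Appendix 1.

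**Inputs (all assumed).** c is the proportion of patients with a glucose-confirmed episode, 5-20%. m is the proportion with a symptom-only entry on glibenclamide, 10-30%. r is the relative reduction of such entries on Xiaoke Pills, 0 or 20-50%. There are 400 patients per arm (sections IV.1-2), ignoring dropout.

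Reported incidence = 1 - (1 - c)(1 - m), with m replaced by m(1 - r) on Xiaoke Pills.

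**No true difference in glucose.** For c = 10%, m = 20%, r = 30%:

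- Glibenclamide: 1 - 0.90 × 0.80 = 28.0%.
- Xiaoke Pills: 1 - 0.90 × 0.86 = 22.6%.
- Risk ratio 22.6/28.0 = 0.81.
- Two-sided 5% test: pooled proportion 25.3%, null standard error √(2 × 0.253 × 0.747/400) = 0.0307. The chance of a false significant benefit is Φ((0.054 - 1.96 × 0.0307)/0.0307) = Φ(-0.20), about 42%.

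| c | m | r | Glibenclamide | Xiaoke | Risk ratio | Chance of p < 0.05 |
|---|---|---|---|---|---|---|
| 10% | 20% | 0 | 28.0% | 28.0% | 1.00 | 5% |
| 20% | 10% | 20% | 28.0% | 26.4% | 0.94 | 8% |
| 10% | 20% | 30% | 28.0% | 22.6% | 0.81 | 42% |
| 5% | 30% | 50% | 33.5% | 19.3% | 0.57 | over 99% |

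The second and last rows are the ends of the range for r of 20-50%. On a glucose-confirmed endpoint both arms have incidence c, so the risk ratio is 1.00 whatever m and r are.

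**Event rates.** With confirmed rate c and symptom-only rate s per patient-year, and 30% relief, the rate ratio is (c + 0.7s)/(c + s). For s/c of 0.5, 1 and 2 it is 0.90, 0.85 and 0.80.

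**Dilution with r = 0.** Take a true confirmed incidence of 10% v 5% (risk ratio 0.50) and m = 20% in both arms. Reported incidence is 28.0% v 1 - 0.95 × 0.80 = 24.0%, a risk ratio of 0.86.

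**Phenotype.** Among control-arm patients classed as having hypoglycaemia, the share with a confirmed episode is c/[1 - (1 - c)(1 - m)]. It runs from 5/33.5 = 15% to 20/28 = 71%. Assume a marker carried by 30% of 800 patients, a true odds ratio of 2 for confirmed episodes, and symptom-only entries unrelated to it. The observed odds ratio is then 1.12 to 1.66 over the same ranges of c and m. At c = 10%, power falls from 81% to 52%, 35% and 25% for m of 10%, 20% and 30%.

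**The case against.** **Attribution is needed.** The definition asks for an episode with symptoms linked to hypoglycaemia, and the table adds quick relief on eating. A reader might infer that any complaint present at entry becomes an episode. The text does not support that: the patient must attribute the complaint to hypoglycaemia, and not every patient has these secondary symptoms. What stands is that such complaints can be logged. Relief on eating separates the two poorly, because ordinary hunger also passes with food.

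**The evidence for differential relief is weak.** The symptom benefit in section I.1 concerns diabetes symptoms in general, from open-label trials whose quality the protocol itself calls poor. The only hypoglycaemia data there are two mild events on Xiaoke Pills and one on glibenclamide among 450 subjects, which does not point towards Xiaoke Pills. Over 4 to 8 weeks, three events are 3/(450 × 4/52) = 0.09 to 3/(450 × 8/52) = 0.04 per patient-year. That trial's definition is not given, so this neither confirms nor refutes the concern. It stands as a reason not to predict bias.

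**Much of the data is already collected.** Glucose is entered with episodes, and the analysis plan may define a confirmed class. Symptoms are scored before treatment (section IX labels this for TCM hospitals), so some baseline adjustment is possible. This largely stands. The gap is that the protocol names no confirmed non-severe class and does not require a reading when symptoms occur. No later plan can recover readings never taken.

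**A broad definition is sensitive, which suits safety.** This stands too, and is why the broad definition should remain for safety recording.

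**Conclusion.** The point holds as a weakness of measurement. Felt symptoms suffice for a non-severe episode, two listed symptoms are shared with the entry syndrome, and no glucose-confirmed class is defined for endpoint 2.1 or goal 2.2. To the extent that symptom-only entries unrelated to glucose occur, they dilute both.

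A reader might go further and infer that the trial will show a spurious safety advantage for Xiaoke Pills, or that its biomarkers are contaminated. The documents do not support either as fact. Bias between arms needs differential relief of palpitations or hunger; without it the test keeps its 5% error rate. Contamination depends on how many symptom-only entries there are and on whether the biomarker work uses them.

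The size is unknown. The risk ratios of 0.57 to 0.94 and the weakened marker odds ratios of 1.12 to 1.66 rest wholly on assumed rates and show only that the effect could matter. Severe hypoglycaemia is little exposed. The change is worth making because it is cheap, not because a large bias has been shown.

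**What to change.** Confine the change to endpoint and biomarker reporting (section III.2 item 2.1 and goal 2.2):

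1. Report glucose-confirmed episodes, by the protocol's own cut-off (below 3.5 mmol/L, or below 3.8 mmol/L plasma), and symptom-only episodes as separate classes.
2. Rest any between-arm hypoglycaemia claim and the biomarker case definition on the confirmed class.
3. Add a diary instruction to take a home meter reading when symptoms occur.
4. Add a sensitivity analysis of the TCM score without the hunger and palpitation items.

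Keep the definition in X.1.4 for safety recording. Termination criterion 5.7 (section V.5) counts hypoglycaemic episodes, so rewording X.1.4 itself could alter that rule. It and all clinical management should stay unchanged.

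The cost is a few lines of text and one diary line, since home metering and the diary card are already in the protocol. The drawback is that true but untested episodes fall into the symptom-only class, so that class must be reported alongside the confirmed one.
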